### Implementation {16c}

The research staff will be responsible for enrolling participants. After participants are enrolled, each participant’s group assignment will be determined by opening a sequentially numbered, opaque, sealed envelope, which will have been prepared in advance by the research staff following the randomization process. The envelopes will only be opened after baseline data collection is complete to ensure allocation concealment.

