### Concealment mechanism {16b}

The allocation sequence will be concealed using a sequentially numbered, opaque, sealed envelope system. After stratified randomization has been conducted in sealedenvelope.com, each participant’s group assignment will be placed in a numbered, opaque envelope. These envelopes will be prepared in advance and will only be opened by the embryologist responsible for embryo handling. The research staff/nurse/clinician responsible for enrolling participants will not be aware of group assignments, ensuring allocation concealment until the interventions are carried out.

After the embryo transfer, if it is determined that the patient is not pregnant, their group assignment may be disclosed to them. However, if pregnancy is confirmed, the group assignment will remain concealed, and the patient will not be informed until a live birth occurs, or in the event of a miscarriage or elective termination. This approach ensures allocation concealment throughout the pregnancy, minimizing bias and maintaining the integrity of the trial.

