### Procedure for unblinding if needed {17b}

This trial is designed to be double-blinded; however, unblinding will be permitted only in cases where it is necessary for participant safety or when a serious adverse event occurs that requires knowledge of the participant’s group allocation to guide clinical care.

If unblinding is required, the following procedure will be followed:The clinical team responsible for the participant’s clinical management will contact the principal investigator (PI).The PI will review the case and determine if unblinding is necessary.If unblinding is deemed essential, the allocation code will be revealed to the care provider.The unblinding event, reason for unblinding, and any actions taken will be documented in the trial records.

Routine unblinding or revealing of group allocations will not occur unless absolutely necessary for participant safety.

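### The protocol names no envelope preparer independent of recruitment, and its section on concealment permits disclosure of allocations that its unblinding section rules out

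*Protocol article*

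**What the plan says.** **Concealment.** Implementation {16c} opens with "The research staff will be responsible for enrolling participants". Its next sentence says that each assignment is found by opening a "sealed envelope, which will have been prepared in advance by the research staff following the randomization process". Concealment mechanism {16b} says "The research staff/nurse/clinician responsible for enrolling participants will not be aware of group assignments" and that the envelopes "will only be opened by the embryologist responsible for embryo handling".

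**Disclosure.** {16b} then adds that "if it is determined that the patient is not pregnant, their group assignment may be disclosed to them". If pregnancy is confirmed, "the patient will not be informed until a live birth occurs, or in the event of a miscarriage or elective termination". Neither permission depends on safety. Procedure for unblinding {17b} allows unblinding only for safety or a serious adverse event, after review by the principal investigator, and ends: "Routine unblinding or revealing of group allocations will not occur unless absolutely necessary for participant safety". Who will be blinded {17a} claims that blinding lasts for the whole trial, with embryologists as the stated exception.

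**The concern.** Opaque, sealed, numbered envelopes conceal the sequence from people who did not fill them. They do not conceal it from the person who did. If that person also recruits, the next assignment can influence who is approached, when, and how a borderline criterion is read. Eligibility here leaves room for judgement, for instance on whether uterine pathology counts as significant. The planned intention-to-treat analysis and covariate adjustment cannot be relied on to remove selection on unmeasured prognosis, so the damage could not be repaired afterwards.

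The disclosure conflict is of a different kind. Staff who follow {16b} would breach {17b}, and a report that says blinding was kept throughout would not describe what participants had been told. A further risk is that past allocations reach recruiting staff or outcome assessors through the participants while the trial is still enrolling.

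**Working it through.** The plan states no figure on this point, so the check is mainly a comparison of texts, followed by a timing calculation.

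**1. Envelopes.**
- Who enrols: the research staff ({16c}).
- Who prepares the envelopes, and when: the research staff, in advance, once randomisation has been run ({16c}).
- Who must not know the assignments: whoever enrols, with research staff named explicitly ({16b}).
- Who opens the envelopes: the embryologist ({16b}).

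The same collective term covers enrolment and preparation in adjacent sentences, and no rule separates the people. Restricting who opens an envelope does not limit what its preparer knows. The assurance in {16b} holds only if preparers and recruiters are different people, and {16c} does not require that.

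**2. Disclosure.**
- {16b}: permitted after a negative result, miscarriage, termination or live birth, with no safety condition.
- {17b}: not permitted unless safety requires it.
- {17a}: blinding kept throughout.

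A standing permission that does not depend on safety is what {17b} excludes. The first two statements cannot both be followed, and the third is inaccurate if the first is used.

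**3. Does disclosure fall within recruitment?**
- Planned enrolment is 578 (Sample size {14}). Recruitment runs from 1 November 2025 to 31 October 2028, which is 36 months (Trial status). The hCG test comes about 2 weeks after transfer ({18b}).
- Even accrual (assumption): 578 / 36 = 16.1 participants per month.
- Two weeks is about 14 / 30.4 = 0.46 month, so about 16.1 × 0.46 = 7.4 participants are enrolled in that time.
- If transfer follows enrolment closely (assumption, since the article gives no interval), all but about the last 7 of 578 would have a first pregnancy result before recruitment closes. A longer interval raises that 7 in proportion.

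So for almost every participant found not pregnant, permitted disclosure could occur while others are still being enrolled. How many would be told cannot be calculated, because the article gives neither the non-pregnancy rate nor how often the permission would be used.

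**4. Can disclosure affect the participant's own result?** At each of the four points in {16b}, her pregnancy outcome is already settled. It cannot.

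**The case against.** The strongest reply on the envelopes is that research staff is a collective noun. The coordinating centre has several distinct roles, including site coordinators, research nurses and data coordinators, and {16b} states outright that those who enrol are unaware of assignments. The full protocol may separate the tasks by person. This stands as far as it goes: the article does not show that the same individuals do both jobs, and concealment is not shown to have failed. But the gap is not a mere omission, because {16c} assigns both tasks in terms that {16b} excludes.

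On disclosure, the reply is that {16b} says only that the arm may be disclosed, to the participant, once her outcome is known. That also stands, and it makes this half the lesser problem. It does not remove the contradiction with {17b}.

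A reader might infer more than the text supports:
- **That all 578 assignments are known to recruiters before consent.** This needs every preparer to recruit and to keep or consult the list. Nothing in the article says so.
- **That 231 to 347 allocations will be disclosed.** That is 578 × 0.40 to 578 × 0.60. It assumes a non-pregnancy rate that the article does not give and treats a permission as universal practice.
- **That later allocations become guessable from blocks.** The article mentions no blocks. Under permuted blocks of 8 down to 2, with all past allocations known at once, correct guesses would average 66.6% to 75.0% against 50%. That is an upper bound, since at least two weeks pass before any disclosure and about 7.4 / 2 = 3.7 further participants per age stratum (equal strata assumed) enter meanwhile. It also requires that telling a participant informs recruiters.

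**Conclusion.** Both conflicts are in the text. The envelope conflict is the serious one: as {16c} stands, a person who both enrols and prepares envelopes could know upcoming allocations, contrary to {16b}. Confidence is high that the passages conflict. Whether anyone will in fact have foreknowledge is unknown, and no size of bias can be derived from the documents.

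The disclosure conflict between {16b} and {17b}, with the related claim in {17a}, is a matter of reconciliation. The double-blind description is not false for the period in which blinding could influence a participant's own pregnancy outcome. What remains is possible exposure of past allocations to staff during a 36-month recruitment, which rests on participants or records passing the information on.

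**What to change.** **In {16c}**, name who prepares and holds the list and envelopes, and require that this person has no recruitment role. A data coordinator already in the coordinating centre would serve. Alternatively, drop the envelopes and have the embryologist, who is unblinded anyway, obtain each allocation online on the warming day from the randomisation service already in use. Either is a reassigned task and a wording change. If recruitment has begun, make the change for all remaining allocations and record who prepared those already used.

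**In {16b}, {17a} and {17b}**, state one disclosure rule. There are two workable options:
- Defer disclosure, for example until recruitment closes. The cost falls on participants: one enrolled in November 2025 would wait up to about 36 months. Waiting until the last outcome is locked would take longer still and is not needed to resolve the conflict.
- Say plainly that a participant may be told her arm once her own outcome is determined, and that this information is kept from recruiting staff and outcome assessors. {17a} and {17b} are then amended to match. The cost is the wording and a simple procedure for who tells the participant.

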## Assignment of interventions: blinding

### Who will be blinded {17a}

This trial will be conducted as a double-blinded study. Both the trial participants and the clinical team will be blinded to the group assignments after the allocation to interventions has been completed. Neither group will have access to information about whether participants are in the intervention group (direct warming method) or the control group (conventional warming method).

Outcome assessors will also be blinded to the group assignments to ensure unbiased evaluation of primary and secondary outcomes, including embryo survival rates, pregnancy rates, and live birth rates. Data analysts will be blinded to the group allocation during the analysis phase to prevent bias in data interpretation.

The use of sequentially numbered, opaque, sealed envelopes ensures allocation concealment until the point of intervention, maintaining blinding throughout the trial.

Embryologists cannot be blinded in this trial.

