### Intervention description {11a}

Intervention group (arm 1): new direct warming methodIn the intervention group, vitrified blastocysts will be thawed using a novel direct warming method. The ready-to-be-thawed blastocyst is placed in a pre-warmed direct warming medium for 1 min. Following this, the embryo is transferred directly into the embryo culture medium in a time-lapse system until it is ready for transfer into the uterus. This new warming method significantly reduces the procedure time to approximately 3 min, making it much faster than the conventional multi-step warming process.Control group (arm 2): conventional multi-step warming methodThe control group will follow the conventional multi-step warming method. In this procedure, vitrified embryos are first placed in a pre-warmed thawing solution for 1–3 min. They are then transferred to a dilution solution for 4–6 min to gradually dilute the cryoprotectants, followed by immersion in a washing solution for 5–10 min to complete the rehydration process. This multi-step method takes approximately 20 min to complete. After thawing, the embryos are placed in the embryo culture medium in a time-lapse system until they are ready for transfer.Blastocysts will be evaluated using the Gardner grading scale with a three-part criterion on blastocyst expansion, inner cell mass (ICM), and trophectoderm (TE) quality. Blastocysts with a score ≥3BB are considered good quality [13].

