**Fig. 1 Fig1:**
[figure not shown]
RCT flowchart

**Table 1 Tab1:** Schedule of the study process

Timepoint	Study period							
	Enrollment	Allocation	Post-allocation					Close-out
	IVF talk	0 week	Embryo transfer	10–14 days	6–8 weeks	20–24 weeks	36–40 weeks	6–8 weeks after birth
Enrollment								
Eligibility screen	X							
Informed consent	X							
Allocation		X						
Interventions								
Administration of different embryo warming methods			X					
Assessments								
Post-thaw embryo assessment			X					
HCG test				X				
Ultrasound of gestation					X			
Phone follow-up						X	X	X

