## Statistical methods

### Statistical methods for primary and secondary outcomes {20a}

All analyses will follow an intention-to-treat (ITT) approach, with statistical significance set at *p* < 0.05 and 95% confidence intervals (CI). Primary outcomes, including embryo survival rate, pregnancy rate, clinical pregnancy rate, and live birth rate, will be analyzed using logistic regression models, adjusting for potential confounders such as cause of infertility, previous ART cycle, and embryo quality. Chi-square tests or Fisher’s exact tests will be used for categorical outcomes like embryo survival, and logistic regression will report odds ratios (OR) for pregnancy and live birth rates.

Secondary outcomes, including implantation rate and multiple gestation pregnancy rate, will be analyzed using generalized linear models (GLM) and chi-square tests. Thawing time will be compared using *t*-tests or Mann-Whitney *U* tests for non-normal data. Cost-effectiveness will be evaluated through cost-effectiveness analysis (CEA), while post-thaw embryo quality will be assessed using standard grading criteria and analyzed with chi-square tests. Missing data will be handled using multiple imputation to maintain the integrity of the results. An extra sensitivity analysis will be conducted if loss to follow-up is more than 5%.

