### Interim analyses {21b}

Given the multi-center nature of this study and the established safety profile of the intervention, no formal Endpoint Adjudication Committee (EAC) or Data Monitoring Committee (DMC) will be established. Instead, the oversight responsibilities for interim analyses and stopping guidelines will be managed by the Trial Steering Committee (TSC).

An interim analysis will be conducted when 50% of the anticipated sample size has been completed, or midway through the trial if any significant safety concerns or deviations from expected outcomes arise. The TSC will review interim results and decide whether to continue, modify, or terminate the trial based on predefined stopping criteria, including serious adverse events directly resulting from the intervention and clear evidence of futility or overwhelming efficacy, such as a 10% embryo survival rate lower than the conventional group. The study team will remain blinded, with only TSC members having access to interim data to ensure unbiased trial conduct.

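### The claim that embryo survival is assessed blind is unsupported and conflicts with embryologists who cannot be blinded

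*Protocol article*

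**What the plan says.** All references are to the protocol article.

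- Who will be blinded {17a} promises masked assessment and names survival: "Outcome assessors will also be blinded to the group assignments to ensure unbiased evaluation of primary and secondary outcomes, including embryo survival rates". The section ends: "Embryologists cannot be blinded in this trial".
- Concealment mechanism {16b} says the envelopes "will only be opened by the embryologist responsible for embryo handling".
- Table 1 (Participant timeline {13}) lists "Post-thaw embryo assessment" in the embryo transfer column, the same column as the warming itself. It names no assessor.
- Intervention description {11a} covers grading in the passive voice: "Blastocysts will be evaluated using the Gardner grading scale with a three-part criterion". It also says that after direct warming "the embryo is transferred directly into the embryo culture medium in a time-lapse system", and control embryos go into a time-lapse system as well. It mentions no reading of images by a masked person.
- Statistical methods {20a} treats survival as primary: "Primary outcomes, including embryo survival rate, pregnancy rate, clinical pregnancy rate, and live birth rate". In Outcomes {12}, the primary list omits survival, and it appears under the secondary outcomes, in the comparison of warming media brands.
- Interim analyses {21b} illustrates the stopping criteria with one number: "such as a 10% embryo survival rate lower than the conventional group".

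**The concern.** Blinded assessment is a property that readers rely on when they judge how far to trust a laboratory endpoint. Here it is claimed for survival by name, while the people who ordinarily work with the embryo at that moment are declared unblindable. If the person who warmed the embryo also records whether it survived, the record is made with knowledge of the arm.

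Two uses of survival give this weight. It is among the outcomes that {20a} analyses as primary, and it is the only measure in {21b} with a number attached for stopping. The Introduction presents direct warming as the team's own method and aims to show that it is at least equivalent to the conventional one. Any leaning by an unmasked scorer would therefore plausibly favour the new method, and would weaken a check meant to detect harm from it. The report would also describe survival as assessed blind when the design gives no basis for saying so.

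**Working it through.** The article gives no figure on this point to reproduce. The main check sets the statements side by side; the arithmetic only shows how sensitive the stopping example is.

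**Can both sentences in {17a} hold?** There are three possible scorers.

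1. The handling embryologist. This person opened the envelope ({16b}) and so knows the arm. The blinding claim for survival is then wrong.
2. Another embryologist. This person could be masked in practice, but {17a} says embryologists cannot be blinded and makes no exception. One of the two sentences would have to change.
3. Someone who is not an embryologist, or who reads coded images. Both sentences could then hold, but no such reader or reading is described. The section on assessment and collection of outcomes {18a} names only general methods.

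So the claim is wrong in the first case, inconsistent with its neighbour in the second, and undescribed in the third.

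**Weight of one embryo at the interim look.** Inputs are 578 participants in total (Sample size {14}) and a look at 50% ({21b}).

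- 578 × 0.5 = 289 participants, and 289 / 2 = 144.5 per arm.
- One embryo: 1 / 144.5 = 0.7 percentage points. Three embryos: 3 / 144.5 = 2.1 points.
- A 10-point shift: 0.10 × 144.5 = about 14 to 15 embryos in one arm.

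**Sensitivity of the 10% example to one-sided scoring.** The article gives no survival rate for the conventional arm and no misreading rate, so these are assumptions: conventional survival s of 95% or 98%, 144 per arm, the threshold read as 10 percentage points, and a share m of true non-survivors in the direct-warming arm scored as survived. With true deficit d, the true direct-arm survival is s − d, and the expected recorded deficit is d − m(1 − s + d). For s = 0.95, d = 0.15, m = 0.25 this is 0.15 − 0.25 × 0.20 = 0.10. The probability that the observed difference reaches 10 points was simulated with binomial draws (400,000 runs per setting).

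| True deficit | m | Expected recorded deficit (s = 95% / 98%) | Probability threshold is met (s = 95% / 98%) |
|---|---|---|---|
| 15 points | 0 | 15.0 / 15.0 | 0.90 / 0.93 |
| 15 points | 25% | 10.0 / 10.75 | 0.49 / 0.58 |
| 15 points | 50% | 5.0 / 6.5 | 0.05 / 0.09 |
| 10 points | 0 | 10.0 / 10.0 | 0.49 / 0.48 |
| 10 points | 25% | 6.25 / 7.0 | 0.12 / 0.12 |
| 10 points | 50% | 2.5 / 4.0 | 0.005 / 0.006 |

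A threshold of this kind depends strongly on even-handed scoring. The table does not say that scoring would be uneven.

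**The case against.** The strongest reply is that nobody is named as the scorer. {17a} treats outcome assessors as a group separate from embryologists, and {16b} gives the envelope only to the embryologist handling the embryo, so a different reader need not know the arm. The shared column in Table 1 fixes the timing and not the person. A journal article may also leave the reader's identity to the full protocol, the case report forms or the centres' operating procedures. This stands as far as it goes: the absence of a named reader is not itself the point. What remains is that two statements in one section, as written, are not reconciled.

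A reader might infer more than the article supports:

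- That survival is established as open-label because embryologists score it. This is a strong inference, but no section says it.
- That a primary outcome is compromised. Only {20a} calls survival primary; Outcomes {12} does not. That disagreement is a separate matter. The blinding claim covers primary and secondary outcomes alike, so the conflict holds under either status.
- That the stopping decision rests on an unblinded call. The 10% figure is introduced as an example, beside serious adverse events, futility and overwhelming efficacy, and the Trial Steering Committee decides.
- That harm has been shown. Three embryos move the difference by 2.1 points against a threshold of 10. The larger effects in the table need true deficits of 10 to 15 points and misreading of 25% to 50% of non-survivors in one arm, none of which comes from the article.

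**Conclusion.** The point holds in a limited form. The claim of blinded assessment for embryo survival is unsupported by anything the article describes, and it conflicts with the unqualified statement about embryologists, the envelope procedure and the timing of the post-thaw assessment. The conclusion rests on the wording alone and not on any assumed rate.

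Its reach is confined to post-thaw survival, re-expansion and grade, and to the use of survival in the interim review. Clinical pregnancy, ongoing pregnancy, live birth and miscarriage, four of the five measures on the primary list in {12}, are not affected. The size of any bias cannot be derived. The arithmetic shows only that each embryo is worth 0.7 points at the halfway look and that, under the stated assumptions, one-sided scoring could sharply reduce the chance of meeting the survival threshold. The wording should be corrected before results are reported; the trial's main comparison does not depend on it.

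**What to change.** In {17a}, limit the blinded-assessor claim to pregnancy and birth outcomes. State that post-thaw survival, re-expansion and grade are assessed unblinded, and label them so in the trial report and in the material the Trial Steering Committee sees at the interim review. This costs a few words of protocol text. The downside is that survival is then presented as unblinded evidence.

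Alternatively, keep the claim if two conditions hold: time-lapse images are stored in a form from which survival can be judged, and a reader who neither opened the envelope nor warmed that embryo is available without added staff. Survival would then be scored from coded images, and {17a} would say so and qualify its sentence on embryologists. The article confirms neither condition; it says only that embryos are cultured in a time-lapse system. This route is therefore optional.

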### Strategies to improve adherence to interventions {11c}

Training and standardization:All embryologists and clinical staff involved in the intervention and control procedures will receive detailed training on the standardized protocols for both the conventional multi-step warming method and the new direct warming method. This will ensure that all procedures are carried out consistently across participants and in line with the trial protocol.Regular monitoring:A dedicated Trial Monitoring Team will be established to observe and ensure protocol adherence throughout the trial. They will periodically review the warming and embryo transfer procedures, both in the intervention and control groups, to identify any deviations from the protocol.Documentation of procedures:For every participant, a detailed record of the warming process will be maintained, documenting the exact steps, time taken, and any deviations from the protocol. This will allow for tracking of adherence and enable prompt corrective actions if any protocol deviations are noted.Adherence audits:Routine audits will be conducted at regular intervals to review all aspects of the trial, including adherence to intervention protocols. These audits will ensure that any potential issues in protocol adherence are identified early and addressed.Participant engagement:Participants will be closely monitored for any concerns or discomfort during the procedure. Regular follow-ups will be scheduled. Any issues will be addressed by the clinical team immediately.By implementing these strategies, the trial aims to ensure high adherence to both the intervention and control protocols while minimizing variability in the procedures administered across the study.

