### Methods for additional analyses (e.g., subgroup analyses) {20b}

Subgroup analyses will be conducted to evaluate the effects of the intervention within predefined groups, such as age (categorized into ≤35 years and >35 years), embryo quality, and cause of infertility. These analyses will help determine if the efficacy of the direct warming method varies across these specific subgroups compared to the conventional multi-step method.

Adjusted analyses will be performed using logistic regression to control for potential confounders, including maternal age, previous IVF cycles, and embryo grading. These adjusted analyses will provide more accurate estimates of the treatment effect on the primary and secondary outcomes.

No additional exploratory analyses are currently planned, though further analyses may be considered based on emerging data trends during the study.

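### The unqualified claim that data analysts are blinded cannot hold for the time and cost analyses; it should be limited to the clinical outcomes

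*Protocol article*

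**What the plan says.** Section {17a} of the protocol article promises: "Data analysts will be blinded to the group allocation during the analysis phase to prevent bias in data interpretation". The only group it exempts from blinding is the embryologists.

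Other sections set out what will be recorded and analysed:

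- **Thawing time, {20a}.** "Thawing time will be compared using" t-tests, or Mann-Whitney U tests if the data are not normal. Either test needs a value for each participant.
- **Procedure records, {11c}.** A record of warming is kept for every participant, "documenting the exact steps, time taken, and any deviations from the protocol".
- **Procedure times, {11a}.** For direct warming: "This new warming method significantly reduces the procedure time to approximately 3 min". For the comparator: "This multi-step method takes approximately 20 min to complete". The two arms also use different solutions.
- **Cost, {12}.** Cost-effectiveness is listed among the primary outcomes. Its consumable, time and labor ratios all place conventional warming in the numerator and direct warming in the denominator.
- **Warming media, {7} and {12}.** Outcomes are to be compared by brand of warming medium.
- **Analysis data, {19}.** The data are coded and stripped of personal identifiers. This protects confidentiality and does not mask the arm.

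**The concern.** The blinding statement covers all analysts and the whole analysis phase, yet at least two planned analyses disclose the arms. Anyone who compares warming times will see which coded group is which. Anyone who computes the cost ratios in the stated direction must already know.

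Blinding the analyst protects decisions that are still open when the data are seen, and this document leaves several open:

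- The adjustment covariates differ between sections. {20a} names infertility cause, earlier ART cycles and embryo quality; {20b} names maternal age, earlier IVF cycles and embryo grade.
- A per-protocol analysis is optional in {20c}.
- Section {20b} allows that "further analyses may be considered based on emerging data trends during the study".

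If these choices are made with the arms visible, the final report would claim a safeguard that was not in place.

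**Working it through.** The plan gives no figure for this point, so there is none to reproduce. The check is whether the variables to be analysed reveal the arm.

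**Step 1: do the stated times overlap?** Inputs are from {11a}. The first conventional step is described as "vitrified embryos are first placed in a pre-warmed thawing solution for 1–3 min". The embryos are then "transferred to a dilution solution for 4–6 min", and the washing step lasts 5 to 10 min.

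- Shortest sum: 1 + 4 + 5 = 10 min.
- Longest sum: 3 + 6 + 10 = 19 min.
- Stated total: about 20 min in {11a}; 15 to 20 min in {6a} and {6b}.
- Direct warming: 1 min in the medium, about 3 min for the procedure.

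The smallest gap is 10 − 3 = 7 min, so the nominal ranges do not overlap.

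**Step 2: can individual participants be classified from time alone?** Take a direct mean of 3 min, a conventional mean T, normal times with a common standard deviation (SD), and a cut halfway between the means. The share misclassified is 1 − Φ((T − 3) / (2 × SD)). The document gives no SD, so values of 1 to 3 min are assumed. Counts are out of the planned 578.

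| T (min) | SD 1 | SD 2 | SD 3 |
|---|---|---|---|
| 20 | 0.0 | 0.0 | 1.3 (0.2%) |
| 15 | 0.0 | 0.8 (0.1%) | 13.1 (2.3%) |
| 10 | 0.1 (0.02%) | 23.2 (4.0%) | 70.3 (12.2%) |

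Example: T = 15 and SD = 3 give (15 − 3) / 6 = 2; 1 − Φ(2) = 0.0228; 0.0228 × 578 is about 13.

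**Step 3: do dummy codes protect the arm labels?** With 289 per arm and an SD of 3 min, the standard error of the difference in means is 3 × √(2/289) = 0.25 min. Even the 7 min gap at the 10 min floor is 7 / 0.25 = 28 standard errors. The coded groups are therefore identified from their mean times, however well single participants can be classified.

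**Step 4: do the cost ratios need the labels?** Each ratio in {12} is conventional over direct. Under codes A and B, an analyst could form A/B and B/A but could not report the specified one without knowing which arm is which.

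**Step 5: set this against {17a}.** The blinding sentence makes no exception for the time or cost analyses. The statement and the planned analyses cannot both stand as written.

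**The case against.** The strongest reply is that nothing says process and clinical fields reach the analyst in one file. Section {19} gives neither a field list nor a release order, and the step-and-time record in {11c} is described as a tool for tracking adherence. Release order, dummy coding and who runs which analysis commonly belong in an analysis plan or data-management plan, which is not shown. This stands. A reader might infer that the blind is lost as soon as the data set is opened, or that no analyst blind is possible. The document supports neither.

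The sentence in {17a} also directly follows one about survival, pregnancy and live birth, so a blind meant for the clinical outcomes is a plausible reading. That is fair, but the wording does not say so.

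The cost ratios use totals over all centers, which could be supplied in aggregate without linking participants to outcomes. This stands too: the ratios need the arms by name but need not expose the clinical data. The 80% saving in {6a} is stated for costs in general, so it should not be read as a consumable-cost difference that separates the arms.

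On harm, pregnancy and live birth are objective, outcome assessors are blinded separately, and {20c} fixes intention-to-treat as primary. The open covariate list and the optional per-protocol analysis could be settled by pre-specification, blinded or not. The allowance for further analyses refers to the course of the study, not specifically to the analysis phase. All this keeps the impact modest.

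None of it rescues the unqualified sentence: whoever runs the thawing-time comparison will know the arms.

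**Conclusion.** The point holds in a limited form. Analyst blinding is stated as covering the whole analysis, but the thawing-time comparison would reveal even coded arms, and the cost ratios require the arms by name. A blind is achievable for the clinical outcomes only, and the text should say so.

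That the coded groups can be recognised rests on the protocol's own times and needs no fine assumption. The share of single participants identifiable from time alone is less certain. It is about 98% or more at the stated totals of 15 to 20 min with an SD up to 3 min, but about 88% if the conventional mean sat at the 10 min floor with an SD of 3 min. A reader might conclude that practically every participant is identifiable. The stated times make a very high share likely, but the document gives no spread, so no exact figure is supported.

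The consequence is modest: the risk lies in discretionary analysis choices, not in how pregnancy or live birth is ascertained.

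**What to change.** In {17a}, limit the analyst-blinding claim to the clinical-outcome analyses: embryo survival, pregnancy, live birth and miscarriage. Then:

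1. Run and lock these analyses under dummy arm codes, on a data set without warming time, step records, warming medium, consumables or cost. Settle the covariates and analysis populations at this stage.
2. Only afterwards release the withheld fields and run the time, cost and warming-media analyses.
3. State in {17a} that this second set is not blinded.

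The cost is a data-management step for the existing Data Management Team and a changed statement in {17a}. There are three drawbacks. The two sets of analyses run one after the other. The adherence flag for any per-protocol analysis must be derived beforehand by someone with access to the step records, so it needs a fixed written rule. The warming-media analyses stay unblinded even where they concern clinical outcomes. If the staged release is not wanted, the minimum correction is to restrict the sentence to the clinical outcomes.
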